**Methods/design:**

In a double blind, placebo controlled, parallel group study, adults (BMI ≥25) with confirmed NAFLD will be randomized to either a 16 g/d prebiotic supplemented group or isocaloric placebo group for 24 weeks (*n* = 30/group). All participants will receive individualized dietary counseling sessions with a registered dietitian to achieve 10 % weight loss. Primary outcome measures include change in hepatic injury (fibrosis and inflammation) and liver fat. Secondary outcomes include change in body composition, appetite and dietary adherence, glycemic and insulinemic responses and inflammatory cytokines. Mechanisms related to prebiotic-induced changes in gut microbiota (shot-gun sequencing) and their metabolic by-products (volatile organic compounds) and *de novo* lipogenesis (using deuterium incorporation) will also be investigated.

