### Oral glucose tolerance test (OGTT)

Participants will consume a standardized menu the day prior to the OGTT to ensure consistency in macronutrient consumption prior to testing. The menu has been designed by a dietitian and includes 3 meals and 2 snacks. Participants will be instructed to finish dinner and then to not eat after 8 pm. The following morning, a baseline blood sample will be taken via a cannula inserted into the antecubital vein. Subsequently, participants will consume a 75 g oral glucose drink and blood samples will be drawn at 30, 60, 120 and 180 minutes. The OGTT will be conducted at baseline and follow-up (24 weeks). Blood will be centrifuged and plasma frozen at −80 °C for future analyses. Glucose will be quantified using a glucose trinder assay (Stan Bio, Boerne, TX, USA) as per our previous work [72].

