### Satiety hormones

At each of the five time points during the OGTT, additional blood samples will be collected for measurement of satiety hormones including insulin. Blood will be drawn into a cooled EDTA vacutainer tube containing diprotinin-A (0.034 mg/ml blood; MP Biomedicals, Irvine, CA); Sigma protease inhibitor (1 mg/ml blood; Sigma Aldrich, Oakville, ON, Canada) and Roche Pefabloc (1 mg/ml of blood; Roche, Mississauga, ON, Canada) [72]. Blood will be centrifuged within 30 min and plasma analyzed for ghrelin (active), insulin, leptin, glucose-dependent insulinotropic polypeptide (GIP) (total), GLP-1 (active), and PYY (total) concentrations using a Milliplex MAP Human Gut Hormone Panel Kit (Millipore, St Charles, MO). Surrogate markers of insulin resistance, HOMA and QUICKI, will be quantified as per our previous work [99].

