### Statistical analyses

Statistical analyses will be performed using SPSS 22.0 software (IBM, Armonk, NY). Values with skewed distribution will be logarithmically transformed prior to analysis. Baseline characteristics will be compared between groups using chi-square for categorical variables and t-tests for continuous variables. Primary analysis will be performed on an intent-to-treat basis, regardless of subject compliance. The primary outcome measures are change from baseline to 24 weeks in hepatic injury (Fibrotest, FibroScan) and liver fat (percent measured by MRI). ANCOVA, with testing for confounding factors (sex) and potential covariates (BMI, age and fasting insulin) will be used to assess the difference between groups at weeks 0 and 24. Should the main effect of diet be significant, Tukey’s multiple comparison test will be used. Secondary outcomes measured at 0 to 24 weeks (e.g. satiety hormones, body fat, glycemia and insulinemia) will be analyzed with ANCOVA as above. For variables measured over time (e.g. body weight, satiety hormones and glucose at 0, 30, 60, 120 and 180 minutes), a mixed model of repeated measures ANCOVA will be applied to examine the effect of treatment, time and their interaction. Our planned secondary analysis will be per protocol with all participants who complete the 24 week intervention and are compliant based on consumption of ≥80 % the product doses. Cases with missing outcome data will be excluded from analysis. Results will be considered statistically significant (2-sided) at *P* ≤ 0.025 (Bonferroni adjustment for 2 primary outcomes).

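### Satiety hormones fall under two analyses with no main one named, and the mixed model as worded has no term for the between-group difference in 24-week change in the OGTT outcomes

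*Protocol article*

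**What the plan says.** All wording below is from the Protocol article.

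- **Statistical analyses, ANCOVA:** "Secondary outcomes measured at 0 to 24 weeks (e.g. satiety hormones, body fat, glycemia and insulinemia) will be analyzed with ANCOVA as above".
- **Statistical analyses, next sentence, mixed model:** "satiety hormones and glucose at 0, 30, 60, 120 and 180 minutes), a mixed model of repeated measures ANCOVA will be applied". Its purpose is "to examine the effect of treatment, time and their interaction". Body weight is another example in the same list.
- **Statistical analyses, covariates:** "ANCOVA, with testing for confounding factors (sex) and potential covariates (BMI, age and fasting insulin) will be used". The baseline value of the outcome is not among them.
- **Oral glucose tolerance test (OGTT):** "The OGTT will be conducted at baseline and follow-up (24 weeks"). After the fasting sample, "blood samples will be drawn at 30, 60, 120 and 180 minutes".
- **Satiety hormones:** "At each of the five time points during the OGTT, additional blood samples will be collected for measurement of satiety hormones including insulin".
- **Abstract, Methods/design:** "Secondary outcomes include change in body composition, appetite and dietary adherence, glycemic and insulinemic responses and inflammatory cytokines".

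**The concern.** There are two linked problems.

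**Overlap.** Satiety hormones appear by name under both analyses, and the Satiety hormones section counts insulin among them. The article does not say which result is the main one. It also does not say whether the ANCOVA uses a fasting value, an AUC or another summary.

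**Time.** The OGTT data have two time dimensions, minute within the test and visit (week 0 or week 24). The mixed model names one time factor, and for these variables only minutes are listed. The abstract defines the glycemic and insulinemic outcomes as changes, so the quantity of interest is the between-group difference in change from week 0 to week 24. A treatment-by-minute term compares curve shapes and does not estimate that difference.

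Glucose tolerance and appetite are named secondary objectives. At stake are the precision of those comparisons and the freedom to choose between two results for the same outcome.

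**Working it through.** The plan states no power or sample size for these outcomes, so there is no figure to reproduce. The check sets the texts side by side and then sizes the possible readings.

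**1. Data against model.** 2 visits × 5 samples = 10 values per hormone per participant. The mixed model as worded has treatment, one time factor (5 minutes) and their interaction. Visit, treatment × visit and the baseline outcome value are not named.

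**2. Readings of the mixed model.** Consider a constant week-24 shift δ in the outcome averaged over the test, with equal variance 1 at both visits and between-visit correlation ρ. The documents give no ρ, so 0.3, 0.5 and 0.7 are assumed. The benchmark is ANCOVA adjusted for the baseline outcome, with residual SD √(1−ρ²). This is not the ANCOVA as stated, which names no baseline outcome covariate.

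- *Both visits pooled, visit ignored.* The treatment effect is (0 + δ)/2 = δ/2, and the SD of the two-visit mean is √((1+ρ)/2). Signal relative to the benchmark: √((1−ρ)/2).
- *Week 24 only.* The effect is δ and the SD is 1. Relative signal: √(1−ρ²).
- *Change from baseline.* The effect is δ and the SD is √(2(1−ρ)). Relative signal: √((1+ρ)/2).

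Set the benchmark at 80% power with two-sided α = 0.025, the plan's level. Its non-centrality is 2.241 + 0.842 = 3.083. Power of each reading is then Φ(3.083 × ratio − 2.241).

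| Reading | ρ = 0.3: ratio, power | ρ = 0.5: ratio, power | ρ = 0.7: ratio, power |
|---|---|---|---|
| Baseline-adjusted ANCOVA | 1, 80% | 1, 80% | 1, 80% |
| Week 24 only | 0.954, 76% | 0.866, 67% | 0.714, 48% |
| Change from baseline | 0.806, 60% | 0.866, 67% | 0.922, 73% |
| Both visits pooled, visit ignored | 0.592, 34% | 0.500, 24% | 0.387, 15% |

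**3. Simulation check.** This used 25 per arm, 2 visits × 5 minutes, α = 0.025 and 4,000 runs. Assumed SDs were 1.0 between participants, 0.5 for visit within participant and 0.5 residual. With a true week-24 shift of 0.60:

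- pooled: estimate 0.31, power 0.11;
- week 24 only: estimate 0.61, power 0.34;
- change: estimate 0.60, power 0.66.

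With no effect and no imbalance, the rejection rates were 0.020, 0.020 and 0.027. The readings therefore differ in what they estimate and how precisely, and none inflates the overall false-positive rate.

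**4. Two results per outcome.** If either of two tests at 0.025 may count, the chance of at least one false positive is 4.9%, 4.7% or 4.0% when the test statistics correlate at 0, 0.5 or 0.8.

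**The case against.** The strongest reply is that the two sentences divide the work. ANCOVA would handle the 0-to-24-week comparison and the mixed model the profile within the test. Curve shape is then what the second model is meant to test, and visit terms, covariance structure and summary measures can be left to an analysis plan that is not shown.

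Much of this stands:

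- Time is generic wording. For body weight, in the same list, it must mean weeks.
- Only satiety hormones are named in both lists. Glycemia could mean fasting glucose or HbA1c, so the glucose overlap depends on interpretation.
- Modelling change from baseline at each minute would be valid and would fit the abstract's definition of the outcomes as changes.
- A week-24-only fit is a valid randomised comparison. Its cost is precision, not bias.

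A reader might infer that the stated model cannot test 24-week change, or that power falls to 34/24/15%. The documents support neither. Those figures apply only if both visits are fitted with visit ignored, which the text does not say will be done. They also rest on assumed correlations and on a comparator that the plan does not state.

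The division-of-work reading does not remove the overlap. The article does not state it, gives no priority between the analyses, and names the same outcomes and model terms explicitly. The objection is to what is written, not to detail left out.

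**Conclusion.** The point holds as a defect of specification. Satiety hormones, and glucose if glycemia means OGTT glucose, have two analyses with no main one designated. For the OGTT variables, the mixed model as worded has no term for the between-group difference in 24-week change, and neither model names the baseline outcome value as a covariate.

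The cost depends on which fit is intended. The two valid readings lose some precision against baseline-adjusted ANCOVA: 48% to 76% power for week 24 only and 60% to 73% for change, where the benchmark has 80%. The one poor reading, pooling without visit, halves the effect. These figures rest on assumed correlations of 0.3 to 0.7, equal variances at the two visits and a constant shift over the test.

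Only secondary outcomes are affected. The primary analysis and the sample size are not. The wording should be changed before analysis because the change is nearly free and removes a choice between two results.

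**What to change.** Designate one main analysis for each OGTT outcome, with the baseline OGTT values in it. Either of these would do:

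1. ANCOVA of a week-24 summary, such as AUC from 0 to 180 minutes, on treatment, adjusted for the same summary at baseline.
2. A curve model of the week-24 values with treatment, minute, treatment × minute, the matching baseline value as covariate and a within-participant covariance.

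A model of both visits with visit added and a test of treatment × visit targets the same difference. If baseline means are left free by arm, its precision is that of the change score. Constraining them to be equal brings it to that of baseline adjustment.

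Label the other analysis supportive, or limit it to fasting values. State whether glycemia means fasting glucose, OGTT glucose or HbA1c.

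The cost is wording only, since all the samples are already planned. The drawback is that AUC alone hides differences in timing within the test, which a supportive curve model would show.

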### Dietary weight loss intervention

All participants will be provided diet and lifestyle counseling in one-on-one sessions with a registered dietitian. Participants will be responsible for buying and preparing their own food. The diet will be designed to achieve a weight loss of 0.5-1.0 kg/week with an appropriate energy deficit based on anthropometrics and indirect calorimetry analysis. Participants will meet with the dietitian for 10 in-person visits (1–2 h each). Nutrition education and behavior modification strategies will be used to reduce intake of total energy, added sugars, sodium, and processed food, and to maintain adequate protein intake. Dietary intake during the phases will be assessed by weighed 3-day food records. The dietitian will also contact participants by phone each week to assess adherence, address questions or issues that arise, and monitor body weight. Body weight and waist and hip circumferences will be measured at each visit, and there will be a fasting blood draw at the midpoint of the study (week 12) to monitor blood chemistries (serum aminotransferases and lipids).

During the first phase (visits 1–4), participants will be provided with two 7-day meal plans designed by the dietitian. Meal plans will be personalized for each participants, taking into consideration lifestyle and food preferences based on questionnaires completed at screening. Nutrition education components will include identifying primary food sources of fat, carbohydrate, and protein, reading nutrition labels, and sources of empty calories. In the second phase (visits 5–8), the focus will be on behavior modification and achieving dietary autonomy. This will be achieved through specific counseling which will include planning and preparing meals in the home, portion control, and choosing foods when dining out. Counseling will also be tailored to each individual, based on initial questionnaires related to food craving and behavior. During the final phase (visits 9 and 10), participants will be entirely responsible for planning their own meals and counseling will focus on maintenance of dietary behaviors.

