### Secondary outcomes

#### Anthropometrics and Dual Energy X-Ray Absorptiometry

Height will be measured at the beginning of the study to confirm BMI. At each dietitian visit, body weight will be measured using a calibrated balance beam scale along with waist circumference and blood pressure. Body composition will be assessed at baseline and week 24 by DXA (Hologic QDR 4500, Hologic, Inc., Bedford, MA).

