### Subjective and objective assessments of appetite

Subjective ratings of appetite will be recorded by participants at home following a meal, at the same time on the same day, each week using a validated 100 mm VAS [96, 97]. The questions asked based on how the participant felt over the past week are:“How hungry do you feel?” anchored by “I am not hungry at all” and “I have never been more hungry”.“How satisfied do you feel?” anchored by “I am completely empty” and “I cannot eat another bite”.“How strong is your desire to eat” anchored by “I have no desire to eat” and “I have a great desire to eat”.“How full do you feel?” anchored by “Not at all full” and “Totally full”.“How much do you think you could eat?” anchored by “Nothing at all” and “A lot”.Over the course of the past week, my appetite was: “Much lower than usual” and “Much higher than usual”.

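### For body weight, the planned mixed-model tests of treatment, time and interaction are poorly aimed at a gradually growing effect; a baseline-adjusted week-24 contrast would serve better (secondary outcomes only)

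*Protocol article*

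**What the plan says.** All references are to the protocol article.

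- **Model.** Statistical analyses introduces the repeated-measures model thus: "For variables measured over time (e.g. body weight, satiety hormones and glucose at 0, 30, 60, 120 and 180 minutes"). For these, "a mixed model of repeated measures ANCOVA will be applied to examine the effect of treatment, time and their interaction". Waist circumference and the appetite ratings are not named there; they belong by extension, because they are also measured repeatedly over weeks.
- **Covariates.** The ANCOVA described just before lists sex, BMI, age and fasting insulin. The outcome's own baseline value is not listed. The text does not say whether baseline enters the mixed model as a response or as a covariate.
- **Separate 24-week analysis.** "Secondary outcomes measured at 0 to 24 weeks (e.g. satiety hormones, body fat, glycemia and insulinemia) will be analyzed with ANCOVA as above". Body weight is not among these examples.
- **Threshold.** "Results will be considered statistically significant (2-sided) at *P* ≤ 0.025 (Bonferroni adjustment for 2 primary outcomes").
- **Schedule.** "Participants will meet with the dietitian for 10 in-person visits" (Dietary weight loss intervention). "At each dietitian visit, body weight will be measured using a calibrated balance beam scale along with waist circumference and blood pressure" (Anthropometrics). Appetite is rated "at the same time on the same day, each week using a validated 100 mm VAS" (Subjective and objective assessments of appetite). The weeks of the dietitian visits are not given.

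**The concern.** For the primary outcomes the section names the quantity of interest, change from baseline to 24 weeks. For body weight it names three model effects instead, and none of them is the difference between arms at the end of treatment.

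- The time effect says nothing about the arms.
- The treatment effect is the arm difference averaged over all visits. If baseline is a response, that average includes a visit at which randomised arms should not differ, and the test carries whatever between-person spread in weight the listed covariates leave.
- The interaction asks whether the curves differ in shape in any way, with roughly one degree of freedom per visit after the first.

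The diet aims at a loss of 0.5-1.0 kg per week. A supplement that helps adherence could therefore plausibly separate the arms progressively, and in that case both between-arm tests can miss a difference that a direct week-24 comparison would find. The trial asks what the prebiotic adds to weight loss alone, so a clear estimate of the between-arm weight difference helps in reading the liver results.

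**Working it through.** **The plan's own figures.** No power is stated for the mixed-model outcomes. The stated sample sizes confirm the n and significance level used below. With n = 2(z₀.₉₈₇₅ + z₀.₈₀)²(SD/δ)² = 2(2.241 + 0.842)²(SD/δ)² = 19.01(SD/δ)²:

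- FibroScan: 19.01 × (4.0/4.1)² = 18.1, so 19
- Fibrotest: 19.01 × (0.056/0.08)² = 9.3, so 10
- MRI liver fat: 19.01 × (5.0/4.4)² = 24.5, so 25

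All three reproduce.

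**Inputs from the article:** 25 per arm, two-sided 0.025, 10 visits.

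**Assumptions, not in the article:** 11 equally spaced weights (baseline plus 10 visits) over weeks 0-24; an arm difference growing linearly to Δ at week 24; no missing data; between-person SD 5, 10 or 15 kg after covariates; and three covariance types:

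- random slopes, SD 0.15-0.25 kg/week, visit error SD 1 kg;
- random walk, 0.8-1.2 kg per √week, visit error SD 0.5 kg;
- compound symmetry, visit error SD 4 kg.

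**Formulas,** with S the covariance matrix of the 11 weights:

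- Week-24 contrast adjusted for baseline: residual variance v = S(24,24) − S(0,24)²/S(0,0); noncentrality Δ²/(v·2/25); F with 1 and 47 df. Δ is set so that power is 80%.
- Treatment term, baseline as a response: mean difference Δ/2, variance of a person's mean over the 11 weights; F with 1 and 48 df.
- Interaction: all 10 successive differences jointly (Hotelling), F with 10 and 39 df.

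**One case in full** (random slopes, SD 10 kg between persons, 0.25 kg/week, error 1 kg):

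- S(24,24) = 100 + 0.25²×24² + 1 = 137 and v = 137 − 100²/101 = 37.99, SD 6.16 kg. SE = 6.16 × √(2/25) = 1.74 kg. Power of 80% needs Δ = 5.52 kg (ratio 3.17).
- Treatment term: 5.52/2 = 2.76 kg. SD of the mean = √(100 + 0.25²×12² + 1/11) = 10.44 kg, SE 2.95 kg, ratio 0.93, **power 9%**.
- Interaction: noncentrality 10.3, hardly more than the 3.17² = 10.0 of the week-24 contrast, but spread over 10 df: **power 33%**.

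**All cases, linear divergence:**

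| Covariance | Δ (kg) | Week-24 contrast | Treatment term | Interaction |
|---|---|---|---|---|
| Random slopes | 3.5-5.5 | 80% | 4-27% | 33-35% |
| Random walk | 3.6-5.3 | 80% | 4-24% | 32% |
| Compound symmetry | 4.5-5.0 | 80% | 5-24% | 62-73% |

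If the covariance is treated as known (10 and 480 df), the interaction rises to 42-46% in the first two rows and 75-85% in the third. Compound symmetry is the least plausible structure for weight-loss curves, because it gives everyone the same underlying slope.

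**A second set-up:** 10 measurement times, correlation 0.5-0.9 between baseline and week 24, and the unadjusted change at week 24 set to 80%. The treatment term has 6-44%; the interaction has 35% under autoregressive correlation and 74% under compound symmetry.

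**Other effect shapes.**

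- Full effect by about week 4, first set-up with the same Δ: the interaction has 99-100% under random slopes or random walk and 55-66% under compound symmetry. A treatment term adjusted for own baseline has 96-100%.
- Late effect (weeks 12 to 24), second set-up: the interaction has 62-85%.
- Linear effect, first set-up, own baseline as covariate: the treatment term recovers to 53-78%.

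**The case against.** The strongest reply is that covariance structure, handling of baseline and the deciding contrast are details that an article leaves to a full protocol or analysis plan not shown here, and that the size above rests on visit weeks, SDs and an effect shape that the article does not give. Much of this stands. The weakness is conditional: an early plateau reverses the ranking, and own baseline as a covariate repairs most of the loss in the treatment term. BMI, sex and age are listed as potential covariates and are stratification factors. They would remove part of the between-person spread and move the treatment term towards the 5 kg case, where it has 13-27%. What remains is that the article does state the model and the effects to be examined, and for a gradual effect those are not the best tests.

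Three stronger readings are tempting, and the documents do not support them.

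- *That glucose and satiety hormones share the problem.* For them the listed times are minutes within the glucose tolerance test, and the preceding sentence gives them a week 0 to 24 ANCOVA.
- *That the false-positive rate doubles.* That needs a rule of claiming an effect if either term is significant. No such rule is stated, and the Bonferroni adjustment is claimed only for the two primary outcomes.
- *That the tests contradict the 6-month objective.* In Specific objectives the 6-month horizon belongs to the primary objective on hepatic injury and liver fat, which is analysed by ANCOVA on weeks 0 and 24.

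**Conclusion.** The point holds in a limited, conditional form, for body weight and by extension waist circumference and weekly appetite ratings. If the arms diverge gradually and baseline is kept as a response, the planned treatment term has about 4-27% power and the interaction about 32-73%, against 80% for a baseline-adjusted week-24 contrast. These figures assume 25 per arm, 11 equally spaced weights, and the SDs and covariances listed above. A reader might infer that the planned tests are weak in general. They are not: for an early plateau one or both can match or beat the contrast. This is a cheap improvement to a secondary analysis, and the primary analyses are untouched.

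**What to change.** Add a sentence to Statistical analyses along these lines: for body weight, waist circumference and weekly appetite VAS, the between-arm comparison is the treatment difference at week 24 estimated from the mixed model, with post-baseline visits as the response, the outcome's own baseline value as a covariate, and treatment-by-visit terms; the interaction and time effects are reported descriptively.

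Cost: one sentence, with the same data and software. The downside is that a difference appearing mid-study and gone by week 24 would be described but not tested.

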### Plasma lipids, liver biochemistry, and inflammatory markers

At baseline, 12 and 24 weeks, a fasting blood sample will be taken for measurement of plasma HbA1c, lipids, CRP, liver enzymes (ALT, ALP, AST), FibroTest, and biochemical markers of liver function (creatinine, electrolytes, albumin, bilirubin). Blood will be drawn at and analysed by Calgary Laboratory Services (Calgary, AB, Canada). Serum adipokines and inflammatory markers (adiponectin, MCP-1, TNF-α, IL-6 and IL-8) will be quantified using Milliplex kits (Millipore, Billerica, MA) from fasting samples obtained at baseline and follow-up (24 weeks) testing.

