### Sample size calculation

Our sample size is based on the primary outcomes of hepatic injury and liver fat. For hepatic injury, we used pilot data from our lab to determine that a sample size of *n* = 19 in each group would have 80 % power to detect a difference in liver stiffness of 4.1 kPa with FibroScan assuming a standard deviation of 4.0 kPa and a 0.025 two-sided significance level. For the Fibrotest [109], a sample size of *n* = 10 per group would have 80 % power to detect a difference in Fibrotest score (0.0 to 1.0) of 0.08 assuming a standard deviation of 0.056 and a 0.025 two-sided significance level. For liver fat measured by MRI [110], a sample size of *n* = 25 per group will have 80 % power to detect a difference in hepatic fat of 4.4 % assuming a standard deviation of 5.0 % and a 0.025 two-sided significance level. Based on these calculations, we will enroll *n* = 25 per group. Assuming a dropout rate similar to that in our previous prebiotic trial [72] of approximately 20 %, we will recruit a total of 60 participants (*n* = 30 per group).

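### The primary analysis is labelled intent-to-treat but drops everyone with a missing outcome, so it is an observed-case analysis of about 48 of 60 randomised participants with no stated check on the loss

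*Protocol article*

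**What the plan says.** Four statements in the Statistical analyses section of the protocol article bear on this.

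- Label: "Primary analysis will be performed on an intent-to-treat basis, regardless of subject compliance".
- Endpoints: "The primary outcome measures are change from baseline to 24 weeks in hepatic injury (Fibrotest, FibroScan) and liver fat (percent measured by MRI"). The ANCOVA "will be used to assess the difference between groups at weeks 0 and 24". Sex is named as a confounder to be tested; BMI, age and fasting insulin are potential covariates.
- Secondary population: "per protocol with all participants who complete the 24 week intervention and are compliant based on consumption of ≥80 % the product doses".
- Missing data, immediately after that: "Cases with missing outcome data will be excluded from analysis". The sentence is not limited to any one analysis.

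The Sample size calculation section aims for 25 per group. It then adds an allowance: "Assuming a dropout rate similar to that in our previous prebiotic trial", put at roughly 20%, "we will recruit a total of 60 participants", 30 per group.

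The repeated-measures mixed model is named for variables measured over time, such as body weight and the glucose-test series. It is not named for the primary measures. The article states no missing-data assumption, imputation or sensitivity analysis for them.

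**The concern.** An intent-to-treat analysis is normally understood to cover everyone randomised. A rule that removes anyone without the outcome gives that up, and here the loss is planned at about a fifth of the sample. This is not a detail left to a separate analysis plan: the article fixes the rule, and the rule conflicts with the property claimed a few lines earlier.

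What is at stake is the comparability that randomisation provides. The article itself gives reasons why loss might be related to outcome, to arm, or to both:

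- NAFLD Treatment ties improvement in steatosis and inflammation to the amount of weight lost, and the Discussion notes how hard weight loss is to achieve. Participants who fail to lose weight and leave may have worse livers than those who stay.
- Prebiotics and the Discussion suggest that the supplement may help adherence through satiety, so retention could be better on prebiotic.
- The supplement is fermented in the gut and is introduced gradually, and bloating and flatulence are tracked (Quality of life and gastrointestinal feelings), so retention could instead be worse on prebiotic.

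Neither on-study weight change nor gastrointestinal tolerance is among the listed ANCOVA covariates.

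**Working it through.** **1. The plan's own sample sizes.** Inputs are from Sample size calculation: two-sided alpha 0.025, power 80%. By the normal approximation, n per group = 2 × (2.2414 + 0.8416)² × (SD/difference)² = 19.01 × (SD/difference)².

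- FibroScan: 19.01 × (4.0/4.1)² = 18.1, so 19.
- Fibrotest: 19.01 × (0.056/0.08)² = 9.3, so 10.
- MRI liver fat: 19.01 × (5.0/4.4)² = 24.5, so 25.

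All three match the article. MRI drives the sample size.

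**2. How many remain.** 60 × (1 − 0.20) = 48, or 24 per group; 12 randomised participants leave the primary analysis. MRI power (noncentral t) is about 76.5% at 24 per group and 78.5% at 25. The power loss is small; the issue is bias.

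**3. Does the exclusion sentence reach the primary analysis?** It follows the per-protocol sentence, so one could try to confine it to that set. But that set already requires completion of 24 weeks, so the sentence would add little there, and its wording carries no limit. The primary ANCOVA also needs an observed week-24 value. The natural reading is that it applies to the primary analysis.

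**4. Possible size of bias.** In one arm, the mean among those observed differs from the mean among all randomised by d × g, where d is the share lost and g is the mean gap in outcome between those lost and those observed. The between-group difference therefore shifts by d₁g₁ − d₀g₀, or (d₁ − d₀) × g if the gap is the same in both arms. The gaps and dropout splits below are assumptions; the article gives none.

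| Dropout by arm | Gap (liver-fat points) | Shift in MRI difference | Share of 4.4 |
|---|---|---|---|
| 20% / 20% | any, same in both arms | 0 | 0% |
| 25% / 15% | 5.0, both arms | 0.10 × 5.0 = 0.5 | 11% |
| 30% / 10% | 2.2, both arms | 0.20 × 2.2 = 0.44 | 10% |
| 30% / 10% | 4.4, both arms | 0.20 × 4.4 = 0.88 | 20% |
| 30% / 10% | 5.0, both arms | 0.20 × 5.0 = 1.0 | 23% |
| 20% / 20% | 5.0, one arm only | 0.20 × 5.0 = 1.0 | 23% |

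The sign depends on which arm loses more. If those lost improve less, heavier loss on prebiotic flatters prebiotic, and heavier loss on placebo counts against it.

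**5. Does the per-protocol analysis act as a check?** It is limited to participants who complete 24 weeks, so it omits those lost before week 24, as the primary analysis does. Comparing the two shows the effect of compliance among those measured, not the effect of the loss.

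**The case against.** The other side has several good points, and they limit the finding.

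- **Bias is possible, not shown.** A reader might infer that the estimate is sound only if data are missing completely at random. That is too strict. Complete-case ANCOVA is also unbiased when missingness depends only on arm and covariates in a correctly specified model, and with equal dropout and equal gaps the shift is zero. What remains is that this condition cannot be taken for granted here.
- **It is not strictly a completers' analysis.** The rule removes missing outcomes, not people who stopped the supplement. Someone who stops but is measured at week 24 stays in, and the article does not say that such people are not followed.
- **The two populations need not nearly coincide.** The per-protocol set also requires at least 80% of doses. The article gives no expected compliance rate, so the overlap is unknown. The narrower point stands: both sets omit those lost.
- **The direction is open.** A reader might infer that the plan favours prebiotic. The article supports routes both ways, including better adherence and generally good tolerance. Nor does it support a claim that the all-randomised effect would be 0.8 × 4.4 = 3.5 points; that assumes that those lost gain exactly nothing.
- **The illustration is generous.** A 5-point gap equals one planning SD and exceeds the target effect.
- **Partial data in the mixed models.** The article does not say whether a case there is a person or an observation, so no waste of data can be claimed.
- **The loss is disclosed.** The trial was openly sized with dropout in mind. That answers the power question, not the bias question or the label.
- **Imputation can be overdone.** Baseline value, three stratifiers, three week-12 markers and ten weights make 17 predictors; fitted separately on 24 per arm, that leaves 24 − 17 − 1 = 6 residual degrees of freedom. This argues for a small model, not for exclusion.

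**Conclusion.** The point holds in this form: the intent-to-treat label and the exclusion rule conflict, and as written the primary analysis is an observed-case analysis. At the article's 20% dropout, it would cover about 48 of 60 randomised participants. Its validity rests on missingness depending on nothing beyond arm and the modelled covariates, an assumption that the article neither states nor tests and that its own account of weight loss and tolerability makes doubtful.

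The size and direction of any bias are unknown. The range of 0.5 to 1.0 points on MRI liver fat (11% to 23% of the 4.4-point target) rests on an assumed 5-point gap in both arms and an assumed 10 to 20 percentage-point difference in dropout. It shows that the effect could matter, not that it will occur. The documents do not support saying that the result will be biased, or biased towards prebiotic.

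**What to change.** Before the data are analysed:

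1. Remove the exclusion rule from the primary analysis. Include all randomised participants, and use every week-24 outcome obtained, regardless of compliance.
2. Handle missing week-24 values by multiple imputation, or by a likelihood-based model that includes the same auxiliary variables. MRI and FibroScan are read only at baseline and week 24 (Primary outcome), so the information must come from other variables already collected. Keep the set small: arm, baseline value, the stratification factors (sex, BMI, age), week-12 ALT and AST, and one summary of weight change. Counting one term for each, that is 8 predictors; fitted to both arms together, it leaves 48 − 8 − 1 = 39 residual degrees of freedom. The week-12 enzymes are already scheduled: "At baseline, 12 and 24 weeks, a fasting blood sample will be taken for measurement of plasma HbA1c, lipids, CRP, liver enzymes". Participants lost before week 12 will lack them, so the procedure must allow for that.
3. Add a missing-not-at-random sensitivity analysis, delta-adjusted, with the deltas allowed to differ by arm because the direction is unknown.
4. Keep the complete-case ANCOVA as a sensitivity analysis.

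At minimum, describe the current analysis as observed-case (modified intent-to-treat) and add item 3.

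The cost is revised wording, a little more analysis work and possibly slightly wider intervals. No new measurement is needed.
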